**3. Subject selection**

**3.1** **Subjects of interest**

Patients

Patients in the East London NHS Foundation Trust, currently treated in a community mental health care team, with a clinical diagnosis of schizophrenia or a related disorder (F20-29).

Key workers

Key workers currently employed in the East London NHS Foundation Trust and working in community mental health teams.

**3.2 Number of subjects**

We will recruit 36 key workers and 180 patients, with 18 key workers and 90 patients in each of the conditions (five patients per key worker). Given the likely drop out of clinicians due to job changes or personal moves, we anticipate the loss of six key workers and 30 of their patients. With a patient drop out rate of less than 10% of the remaining 150 patients (as in the original trial it was less than 10% over a one year period) we will end with a sample of 136 patients. Assuming a practically negligible cluster effect (as in the original trial) the sample size will be sufficient to detect a medium effect size of 0.5 (Cohen’s D) with 80% power at the 5% significance level. A slightly higher effect of 0.57 will be detected with 90% power. The effect size of 0.5 would require that at the end of the intervention patients in the experimental group rate their satisfaction with at least 3 out of 12 life domains in the MANSAat least one point higher than patients in the control group. The sample size will also be sufficient to provide the required variation of experiences for addressing all other research questions.

Out of the caseload of all potentially eligible patients, we will randomly select 7 patients (allowing for 2 patients not fulfilling the inclusion criteria or not consenting to participate) per key worker. The remaining patients on the caseload of each key worker will be randomly ranked. They will be approached one-by-one if and when there is a need to recruit more patients for the given worker (e.g. in case more than 2 of the originally selected 7 do not consent to participate). Once all patients for one key worker have been recruited, the key worker will be randomly allocated to the intervention or control condition and receive either the training for DIALOG+ or the instructions for the control condition.

**3.3 Inclusion criteria**

To reflect the pragmatic nature of the trial, there will be wide inclusion criteria and very few exclusion criteria for both clinicians and patients. The inclusion criteria for patients will be wider than in the original DIALOG trial to test whether patients with more acute disorders, who have not been in care for many years and whose treatment in secondary services may not continue for another year, can also be recruited.

Patients

- Treatment in a community mental health care team in the NHS for at least one month;
- No planned discharge for the next six months;
- Clinical diagnosis of schizophrenia or a related disorder (F20-29);
- Age between 18 and 65 years; A mean score of lower than 5 on the MANSA;
- Capacity to give informed consent.

Key workers

- Professional qualification as a clinician (nurse, social worker, psychologist, occupational therapist, doctor);
- More than 6 months experience of working in community mental health care;
- Working as care coordinator.

**3.4 Exclusion criteria**

Patients

- Insufficient command of the English language for conducting meetings in English and filling in the assessment instruments of outcomes;
- A mean score of 5 or more on the MANSA;
- Learning difficulties.

Key workers

- None.

**4. Study procedures**

**4.1 Informed consent procedures**

Patients will be recruited from CMHTs in East London NHS Foundation Trust. Researchers will contact teams via e-mail and/or telephone to arrange a meeting to present the study to key workers, managers and consultant psychiatrists, and involving the leads at each site. One week after these meetings, a decision on participation will be sought. Written informed consent to participate will be obtained from individual key workers.

Clinicians, supported by research and administrative staff, will identify patients on their caseloads fulfilling the inclusion criteria, then ask suitable patients for consent to be approached by a researcher. If the answer is yes, a research assistant will provide an information sheet and arrange a meeting with the patient to discuss the project in full (at least two days later). At the meeting, the researcher will go through the information sheet, explain the study, obtain written informed consent, and establish all inclusion criteria. Once all patients (maximum of seven) from one clinician have consented, the clinician (and correspondingly, the clinician's patients) will be randomly allocated to either the intervention or control group. Randomisation will be done by an independent statistician at the Pragmatic Clinical Trials Unit (PCTU) through e-mail.

**4.2** **Data collection**

Data will be collected by the research assistants on the EPOS programme (NIHR Programme for Applied Research within which the trial will be conducted). We will seek adoption of the study on the Mental Health Research Network so that recruitment and baseline data collection can be supported by Clinical Scientific Officers of the MHRN. The researchers will keep ongoing contact with the clinicians and patients involved. There will be masking of researchers with respect to which group, intervention or control, the patients and clinicians belong to. For the assessment of the primary outcome at the end of the 6 month intervention period, they will be supported by other researchers in the Unit for Social and Community Psychiatry.

**4.3 Data management**

Data will be managed locally in the Unit for Social and Community Psychiatry complying with the standard operating procedures (SOPs) of the PCTU. The research assistants on the EPOS programme will be in charge of the data management on a day-to-day basis. Monitoring, quality assurance and archiving will also be conducted in accordance with the SOPs of the PCTU.

**4.4 Confidentiality**

All hard copies of data will be stored in a secure locked filing cabinet accessible only to the members of the project team. All electronic data will be stored on NHS or university computers, and patient identifiable information will be omitted upon data entry. Restricted access permission will be obtained for any documents containing patient identifiable information and these will be stored separately from the anonymised database. Only members of the project team will have access to this information. Video recordings and audio recordings will be stored in locked cabinets when not in use by the researchers. These recordings will only been seen/heard by members of the research team at the Academic Unit of Newham Centre for Mental Health and will not be played to anyone else. We will anonymise patients in the video recordings through blurring of faces.

**4.5 Compensation of participants**

Key workers

Key workers will participate in this research during their regular office hours and as part of their contracted work with the NHS Trust.

Patients

Patients will be paid £20 per clinical interview or focus group.

**4.6 Schedule of treatment**

In both the experimental and the control condition, patients will receive the given treatment condition, i.e. DIALOG+ or the independent rating of the DIALOG scale on an iPad, once per month for six consecutive months.

**4.7 Subject Withdrawal**

Participants will be informed through their consent forms that they are free to withdraw from the study at any time, without consequence, without having anything related to their services/employment affected. This fact will be emphasised by the researcher in all discussions explaining the study and prior to taking informed consent.

**4.8 End of Study Definition**

The end of the study will be when all project data for all patients and clinicians has been collected subsequent to the 6-month follow-up period, and data analysis is complete.

**4.9 Governance**

The trial will be subjected to all procedures of research governance in the participating NHS Trusts. The Trial Steering Committee is chaired by [name] (King’s College London). Further members are [name] (University of Ulm, Germany), [name] (King’s College London), [name] (University of Oxford) and [name] (University of Lund, Sweden). A Data Monitoring and Ethics Committee will be established and the membership agreed with the Trial Steering Committee.

**5. Analysis**

Quantitative data will be analysed descriptively and by comparing outcomes in the two groups. Our primary analysis will be a strict intention-to-treat analysis or an available case analysis following intention-to-treat principles. Which analysis is used will depend on the number of missing values, the validity of any necessary assumptions (which may be particularly uncertain in this case) and the ease of multiple imputation (which will be used for the intention-to-treat analysis) given the analysis model. Currently, multiple imputation is, for example, much less straightforward if we opt for generalised estimating equations as our model of analysis. A decision about strict intention-to-treat or available case analysis will be made and written into a full analysis plan before any analysis is undertaken and before data are unblinded.

We intend to use generalised linear models as appropriate to the outcome, with fixed effects for the intervention and random effects for clinician (to adjust for the cluster effect of several patients treated by the same clinician). At end of treatment we expect missing data to be minimal. We will use sensitivity analyses to explore the impact of missing data.

Videotapes will be analysed according to specific criteria for adherence to manual. Audiotapes from focus groups will be analysed using thematic analysis.

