Clinicians will be recruited from CMHTs in East London NHS Foundation Trust. Once clinicians have been recruited, patients meeting the eligibility criteria will be identified on their caseloads and randomly selected for participation in the study. Patients will then be asked by the clinicians for consent to be approached by a researcher. If patients consent, a researcher will contact them, do the baseline assessment and check all inclusion criteria. Due to ceiling/floor effects, patients who score very favourably on the primary outcome at baseline render a substantial improvement unlikely if not impossible. Therefore, patients who rate their mean subjective quality of life on the Manchester Short Assessment of Quality of Life (MANSA) (12) as 5 (satisfied) or higher will be excluded. Once five patients (per clinician) meeting the inclusion criteria have been recruited, the clinician – and correspondingly, his/her patients – will be randomly allocated to either the intervention or control group. Clustering of clinicians will prevent contamination effects in the study. Randomisation will be done by an independent statistician at the Pragmatic Clinical Trials Unit (PCTU) through e-mail.

Outcomes

Outcomes will be assessed at baseline and after 3, 6, and 12 months. We will attempt to keep the researchers assessing the outcomes masked about the allocation of the patients. If masking of the interviewer cannot be maintained, we will put researchers working at the Unit for Social and Community Psychiatry at the Newham Centre for Mental Health who are independent of the core research team)into contact with patients via telephone for conducting the assessment of the primary outcome and, as far as feasible, secondary outcomes. In such cases, patients will be asked not to discuss the treatment they received for the duration of the call.

The primary outcome will be subjective quality of life, measured on the MANSA (as in the original trial).

Secondary outcomes for the trial will consist of:

- Recovery as measured on the severity parts of each of the 24 items of the CHOICE scale(13) (satisfaction, i.e. the second part of each item, is already assessed on the MANSA)
- Objective Social Outcomes (SIX) (14), also assessed using the MANSA (sections 2 and 3), at 6 and 12 months only
- Social contacts in the last week in a structured interview
- Treatment Satisfaction on the Client Satisfaction Questionnaire (CSQ-8) (15)

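### The stated analysis model names no baseline term, although baseline MANSA is measured on every eligible patient before randomisation; adding it would gain precision at almost no cost

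*Protocol*

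**What the plan says.** Protocol section 5 (Analysis) introduces the model as an intention: "We intend to use generalised linear models as appropriate to the outcome", "with fixed effects for the intervention and random effects for clinician". It explains the random effect as the means of handling several patients sharing one clinician. It names no covariate, change score or adjusted analysis, and neither does any other section. The same section still mentions generalised estimating equations as a possibility ("if we opt for generalised estimating equations as our model of analysis"). It says that the choice between strict intention-to-treat and available-case analysis will be "written into a full analysis plan before any analysis is undertaken and before data are unblinded".

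On the outcome, section 2.2 states: "The primary outcome will be subjective quality of life, measured on the MANSA". On timing it states: "Outcomes will be assessed at baseline and after 3, 6, and 12 months". Section 3.3 makes "A mean score of lower than 5 on the MANSA" an entry condition, and section 3.4 mirrors it as an exclusion. Under the allocation heading of section 2.2, the baseline assessment and the eligibility check come before the clinician is randomised. Every eligible patient therefore has a pre-randomisation value of the primary outcome.

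Section 3.2 sizes the trial on Cohen's d between groups at the end of the intervention: 136 analysed patients, d = 0.5 "with 80% power at the 5% significance level", and 90% power at d = 0.57. It uses no baseline correlation.

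**The concern.** Someone who fitted the model exactly as written would compare follow-up MANSA scores between arms with no reference to where each patient started. Two things would be lost.

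The first is precision. The part of the follow-up variance that baseline predicts stays in the residual and widens the confidence interval.

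The second is protection against chance imbalance. Allocation is by clinician, with 36 clinicians, and the protocol describes no stratification or balancing on baseline MANSA. The model is therefore the natural place to deal with a chance difference between arms, and as written it does not.

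The usual reasons for leaving baseline out are absent. The value is already collected, and entry requires it, so the covariate should not be missing.

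**Working it through.** **Inputs from the protocol (section 3.2).** 136 analysed patients, taken as 68 per arm; 30 clinicians remaining (36 less 6), so 136/30 = 4.53 patients per clinician; d = 0.5 and 0.57; 5% level, taken as two-sided because sidedness is not stated; clustering treated as negligible.

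**Assumed inputs.** The baseline to follow-up correlation r of the MANSA is not given; the range 0.2 to 0.6 is used. The cut at a mean score of 5 narrows the baseline range and may lower r, so the low end must be taken seriously. No intraclass correlation (ICC) is given; 0 is used first, then 0.02 and 0.05.

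**Step 1: reproduce the stated power without baseline.** Noncentrality = d × √(n/2) with n = 68 per arm. For d = 0.5 this is 0.5 × √34 = 2.915. With 134 degrees of freedom, power is 82.5% (83.0% by the normal approximation). For d = 0.57 it is 0.57 × √34 = 3.324, and power is 91.0%. Both stated figures are met.

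**Step 2: add baseline.** Adjustment multiplies the residual variance by 1 − r², so d is replaced by d/√(1 − r²). With d = 0.5, 68 per arm and ICC 0:

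| r (assumed) | 1 − r² | d/√(1 − r²) | Power | Unadjusted patients for the same precision, 136/(1 − r²) |
|---|---|---|---|---|
| none | 1.00 | 0.500 | 82.5% | 136 |
| 0.2 | 0.96 | 0.510 | 84.0% | 142 |
| 0.3 | 0.91 | 0.524 | 85.9% | 149 |
| 0.5 | 0.75 | 0.577 | 91.7% | 181 |
| 0.6 | 0.64 | 0.625 | 95.1% | 213 |

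The degree of freedom spent on the covariate does not change these figures to one decimal place.

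**Step 3: allow some clustering.** The design effect is 1 + (4.53 − 1) × ICC. The t reference has 30 − 2 = 28 degrees of freedom, and the same ICC is kept after adjustment.

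- ICC 0.02: design effect 1.071. Power is 77.6% unadjusted, 81.4% at r = 0.3 and 88.1% at r = 0.5.
- ICC 0.05: design effect 1.177. Power is 73.7% unadjusted and 85.0% at r = 0.5.

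**Step 4: how much chance imbalance to expect.** With 68 per arm and ICC 0, the standard error of the baseline difference is √(2/68) = 0.171 SD. A difference beyond 0.2 SD in either direction has probability of about 24% (28% at ICC 0.05). With all 180 patients the standard error is √(4/180) = 0.149 SD, and a difference beyond 0.3 SD has a probability of about 4% (about 7% at ICC 0.05, design effect 1.2). A moderate imbalance is thus quite possible and a large one is unlikely. An imbalance of 0.2 SD carries an expected r × 0.2 SD into an unadjusted estimate: 0.04 SD at r = 0.2 and 0.12 SD at r = 0.6, against a target effect of 0.5 SD.

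**The case against.** The strongest objection is that the model sentence states an intention and is not a closed specification. It does not say that the intervention is the sole fixed effect, it leaves another model type open, and a full analysis plan is announced. Covariates are often fixed in such a plan. This stands in part. A reader might infer that the trial has decided on an unadjusted primary analysis and disregards baseline; the protocol does not establish that. It does, however, name the model's fixed and random terms, and what it expressly defers is the handling of missing data, not covariates. Improving the model that is written is therefore a fair request.

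Second, nothing stated is wrong. Under randomisation the unadjusted comparison is valid, and section 3.2 never relied on baseline adjustment. This stands in full. A reader might infer that the trial is underpowered without the covariate; on the protocol's own assumption of negligible clustering, step 1 shows that it is not.

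Third, the size of the gain depends on an r that the document does not give. This also stands: at r = 0.2 the gain is only 1.5 percentage points. Baseline MANSA may well be the best predictor of follow-up MANSA, but the protocol contains no figure to show it.

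Fourth, a reader might infer that serious baseline imbalance is likely with so few clinicians. Step 4 does not bear that out: beyond 0.3 SD the chance is about 4% to 7% with 180 patients.

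Last, adjusting every secondary outcome for its own baseline does not fit the text, because section 2.2 lists the objective social outcomes index (SIX) at 6 and 12 months only. The recommendation has to be limited accordingly.

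**Conclusion.** The point holds as a worthwhile improvement. The model as stated has no baseline term, although baseline MANSA is available for every eligible patient. Adding it would raise power at d = 0.5 from 82.5% to between 84.0% and 95.1%, for 136 patients, ICC 0 and an assumed r of 0.2 to 0.6. It would also take the part of the estimate due to chance baseline difference out of the comparison.

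The gain matters most if clustering is not quite negligible. At an assumed ICC of 0.02 with cluster-based degrees of freedom, unadjusted power is slightly below 80%, and adjustment at r = 0.3 brings it back above. Both r and the ICC are assumptions, so the direction of the benefit is secure but its size is not. Neither the validity of the analysis nor the stated power under negligible clustering is in question.

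**What to change.** In section 5, extend the model sentence so that the primary model includes the patient's baseline MANSA mean score as a fixed covariate, alongside the intervention and the random clinician effect. Put the same statement in the full analysis plan before unblinding, so that the choice between adjusted and unadjusted results cannot be made after seeing the data. For each secondary outcome, include its own baseline value where one is collected; for SIX, state whether a baseline value exists, since section 2.2 lists it at 6 and 12 months only. The sample size need not change.

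The cost is one sentence of text and one degree of freedom per model, with no extra data collection for the primary outcome.

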**6. Publication Policy**

Data from this study will be anonymised and used in publications for peer reviewed scientific journals, conference presentations and publication on the Queen Mary University of London web site.

